### 2.2. Study Population

The target population consists of adult patients (≥ 50 years) with a previous diagnosis of COPD presenting to the ED with an acute exacerbation requiring evaluation and management. Acute exacerbations will be defined according to the Rome Proposal, which defines an acute exacerbation as an event characterized by worsening dyspnea and/or cough and sputum over ≤14 days, often accompanied by tachypnea and/or tachycardia, and associated with increased local and systemic inflammation and physiological deterioration [18,19]. Exacerbation severity will be classified at the point of care as mild, moderate, or severe according to the Rome Proposal severity classification, based on objective clinical, physiological, and inflammatory parameters assessed at ED presentation [18,19]. Patients enrolled in the study will have a prior diagnosis of COPD, with GOLD spirometric grade and ABE category assessment established according to current GOLD recommendations at the Pneumology Clinic. The GOLD spirometric grades (I–IV) classify the physiological severity of airflow obstruction and are defined based on post-bronchodilator forced expiratory volume in 1 s (FEV_1_) expressed as percent predicted. This spirometric grading remains a fundamental descriptor of disease severity and is essential for the diagnostic characterization of COPD. Category A includes patients with low symptom burden and low risk of exacerbations. Category B includes patients with increased symptoms but low risk of exacerbations. Category E includes patients at high exacerbation risk, irrespective of the level of symptoms [3] (Table 2).

Patients presenting with conditions that mimic an acute COPD exacerbation will be excluded from the study. These include acute heart failure, acute coronary syndromes, major arrhythmias, pulmonary embolism, pneumothorax, acute asthma exacerbation, non-pulmonary sepsis, upper airway obstruction, and respiratory infections in patients without previously documented COPD. Additional conditions that may interfere with respiratory function and therefore lead to exclusion from the study are detailed in Table 3. In patients presenting to the ED with a previously confirmed diagnosis of COPD, infections such as pneumonia, bronchitis, or viral illnesses will be considered valid triggers of an acute exacerbation [18,19].

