### 2.3. Sample Size and Study Duration

The study is planned to include approximately 100 consecutive eligible patients admitted over a 15-month period. The sample size was estimated based on local patient volumes and previous annual ED statistics (over 600 COPD admissions per year), ensuring sufficient statistical power to detect correlations between biomarker levels and clinical outcomes. Baseline biomarker values will be analyzed exclusively for prognostic correlation with the later need for oxygen therapy, NIV or IMV, and will not be used to guide acute therapeutic escalation or de-escalation.

Based on an estimated annual number of approximately 600 COPD presentations to the ED, we anticipated enrolling around 100 eligible patients meeting the study inclusion criteria. In these participants, five biomarkers (resistin, CC16, IL-6, TNF-α, and S100β protein) will be measured and correlated with disease severity and short-term outcomes.

A post hoc power analysis performed using G*Power software (version 3.1.9.7) for a two-tailed Mann–Whitney test, assuming a large effect size (Cohen’s d = 0.8) and a Bonferroni-adjusted significance level (α = 0.01), indicated a statistical power (1 − β) of approximately 0.91–0.92. This suggests that a sample size of 100 participants could be adequate for detecting large and clinically relevant differences in biomarker levels between well-defined severity or outcome groups. In patients with acute exacerbations of COPD, Vassiliou et al. reported higher serum resistin levels during the acute phase as compared to the stable phase after clinical recovery (median at admission 19.44 ng/mL vs. 9.70 ng/mL at follow-up), indicating a large difference between clinically distinct states [4]. We will reevaluate the sample size after enrollment of 20 patients, and we plan to extend the study to other centers, if necessary.

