#### 2.5.2. Recorded Data

Demographic data: age, sex, place of residence (urban or rural), living conditions (home or long-term care facility), past medical history, chronic medication, hospitalization within the previous 30 days, and classification as end-stage or palliative care prior to ED admission will be recorded in the patient monitoring form at admission.

Parameters evaluated during the study at ED admission: systolic and diastolic blood pressure (SBP/DBP), mean arterial pressure (MAP), core temperature (T°C), Glasgow Coma Scale (GCS) score, blood glucose, urine output, peripheral oxygen saturation (SpO_2_), end-tidal (Et) carbon dioxide (CO_2_)—EtCO_2_ and EtCO_2_ trend; oxygen therapy requirements [(mask type, O_2_ flow rate per minute, Fraction of Inspired Oxygen (FiO_2_)]; need for NIV with ventilatory parameters; need for IMV with ventilatory parameters, including airway resistance and lung compliance; requirement for vasoactive support; and medication administered in the ED.

Laboratory data collected at ED admission: routine laboratory investigations will be performed at ED admission and will include a complete blood count, serum creatinine, urea, liver enzymes [Alanine Aminotransferase (ALT) and Aspartate Aminotransferase (AST)], total bilirubin, blood glucose, and a standard coagulation profile. Arterial blood gas analysis will be conducted to assess potential of hydrogen (pH), lactate, bicarbonate (HCO_3_^−^), partial arterial pressures of oxygen (PaO_2_) and carbon dioxide (PaCO_2_), fraction of inspired oxygen (FiO_2_), the PaO_2_/FiO_2_ ratio, the end-tidal to arterial CO_2_ gradient (EtCO_2_–PaCO_2_), and the alveolar—arterial oxygen difference (A–aDO_2_). Additional analyses well comprise sepsis and infection biomarkers [C-reactive protein (CRP), procalcitonin, and fibrinogen], cardiac dysfunction biomarkers [high-sensitivity troponin I (hs-cTnI) and N-terminal-pro–B-type-Natriuretic-Peptide (NT-proBNP)], and the thrombosis marker D-dimer.

Imaging studies performed at ED admission: Imaging studies well be performed at ED admission according to clinical indications and will include chest radiography, chest computed tomography (CT), and lung ultrasound examinations. In selected cases, diaphragmatic motion and compliance will also be assessed by bedside ultrasonography to evaluate respiratory mechanics and ventilatory function.

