#### 2.5.4. Data Monitoring

At ED admission, all patients will undergo assessment using validated severity and prognostic scores available on the MDCalc platform (www.mdcalc.com). The following tools will be applied: mMRC Dyspnea Scale for grading dyspnea severity, the SOFA score, GCS, for evaluating neurological impairment secondary to hypoxia or hypercapnia, and the CFS, adapted for triage levels used in Romania, to estimate frailty and predict mortality. Additional prognostic scores specific to COPD will be applied, including the Ottawa COPD Risk Scale (predicting 30-day mortality or severe adverse events such as myocardial infarction or the need for intubation), the DECAF Score for in-hospital mortality in acute exacerbations of COPD, and the BAP-65 Score for in-hospital mortality prediction.

Serum biomarker levels will be measured according to the previously described analytical protocol. Based on clinical status and therapeutic requirements, study participants will be classified into three groups: COPD patients requiring supplemental oxygen therapy, those requiring NIV, and those requiring IMV. These measurements are intended solely to establish prognostic associations with subsequent respiratory support requirements and will not influence real-time clinical management.

At discharge from the ED or before hospitalization in the Pulmonology Department or the Internal Medicine Department, patient outcomes will be documented as improved (reduction in dyspnea and clinical instability, no requirement for escalation of respiratory support, decreased level of respiratory support, and evidence of improving gas exchange), stable (no significant improvement but no deterioration, with the same level of respiratory support maintained), worsened (increased respiratory distress, need for escalation of respiratory support, and worsening gas exchange or hemodynamics), or deceased (ED mortality). The total duration of hospitalization will be recorded, as well as survival time, including the date of death if it occurred during the ED stay or hospitalization. Early survival will additionally be assessed at 28 days through telephone follow-up.

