## 3. Expected Results and Anticipated Discussion

In this study, we expect to identify a composite biomarker profile-combining resistin, CC16, IL-6, TNF-α, and S100β-that improves early prognostic assessment in AECOPD beyond established clinical scores and routine laboratory indicators. It is important to emphasize that biomarker measurements obtained at ED admission are used exclusively as early prognostic indicators. Their purpose is to examine whether higher baseline levels predict progression to supplemental oxygen, NIV, or IMV, without influencing therapeutic decisions during hospitalization.

Three pre-specified findings are anticipated:Early biomarker–outcome correlations.

Higher admission levels of inflammation and injury biomarkers are expected to correlate with the need for ventilatory escalation, prolonged hospital stay, and increased 28-day mortality. Prior studies demonstrated that pro-inflammatory cytokines-particularly IL-6 and TNF-α- rise during acute exacerbations and are associated with clinical deterioration, frequent relapses, and mortality, supporting their role as prognostic markers in acute care models [14,15].

In COPD cohorts, resistin levels increase during exacerbation and decline upon recovery, mirroring systemic inflammatory burden and multi-organ stress [4,5,10,11]. These dynamics suggest its potential as a broad indicator of systemic inflammation in AECOPD [6].

II.Added value over clinical scores.

We expect incremental prognostic accuracy when integrating biomarker panels with validated Emergency Department risk tools such as DECAF [7], Ottawa COPD Risk Scale [9], and BAP-65 [8]. This integration could enhance discrimination and calibration for early triage decisions (e.g., progressive escalation from oxygen therapy to non-invasive ventilation, and ultimately invasive mechanical ventilation) and inform safer de-escalation strategies. While these scores already predict short-term outcomes effectively, adding an objective biological layer may refine their real-time predictive performance and improve individualization of care in the ED.

III.Mechanistic read-outs with management implications.

Lower CC16, a marker of bronchiolar epithelial integrity, has been causally associated with increased COPD susceptibility and faster progression in Mendelian randomization analyses [6]. In the acute setting, reduced CC16 concentrations may reflect extensive epithelial damage and predict more severe trajectories in AECOPD [12,13].

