## Figures and Tables

**Table 1 diagnostics-16-00122-t001:** Objectives proposed by the research team.

Primary Objective	Secondary Objectives
To evaluate the association between serum levels of resistin, CC16, IL-6, TNF-α, and S100β measured at ED admission and early outcomes, including discharge status and 28-day survival, in patients presenting with acute exacerbations of COPD (AECOPD).	To determine biomarker cutoff values associated with the need for escalation of respiratory support (oxygen therapy, non-invasive ventilation, or invasive mechanical ventilation).
	To identify combinations of circulating biomarkers and established clinical scores that best predict short-term mortality and organ dysfunction.
	To assess the relationship between diaphragmatic contractility evaluated by bedside ultrasound and circulating biomarker levels, in relation to the level and duration of ventilatory support.
	To explore the potential role of biomarker-based risk stratification in informing clinical decision-making for AECOPD patients in the ED.

Legend: CC16—club cell secretory protein 16; IL-6—interleukin-6; TNF-α—tumor necrosis factor-alpha; S100β—S100 calcium-binding protein beta; ED—Emergency Department; COPD—chronic obstructive pulmonary disease; AECOPD—acute exacerbation of chronic obstructive pulmonary disease.

**Table 2 diagnostics-16-00122-t002:** Inclusion criteria for eligible study participants.

Inclusion Criteria	
Age ≥ 50 years. Confirmed prior diagnosis of COPD, regardless of disease stage or ongoing therapy:	
(a) the GOLD spirometric grades	GOLD I (FEV_1_ ≥ 80%) GOLD II (50% ≤ FEV_1_ < 80%) GOLD III (30% ≤ FEV_1_ < 50%) GOLD IV (FEV_1_ < 30%)
(b) ABE category assessment	A—low symptom burden and low risk of exacerbations; 0–1 moderate exacerbations in the previous year, with no hospitalizations B—increased symptoms but low risk of exacerbations; 0–1 moderate exacerbations in the previous year, without hospitalization E—high exacerbation risk, defined as ≥ 2 moderate exacerbations or ≥1 exacerbation requiring hospitalization in the previous year, irrespective of the level of symptoms
Admission to the ED with acute exacerbation of COPD. Signed informed consent obtained from the patient or legal representative.	

Legend: COPD—chronic obstructive pulmonary disease; GOLD—Global Initiative for Chronic Obstructive Lung Disease; FEV_1_—forced expiratory volume in 1 s; ED—Emergency Department.

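### The respiratory-support classification has no level for patients who never need oxygen, so need for oxygen, a stated outcome, has no comparator within it

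*Protocol article*

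**What the plan says.** **Classification.** Section 2.5.4 states that "study participants will be classified into three groups: COPD patients requiring supplemental oxygen therapy, those requiring NIV, and those requiring IMV". The lowest level is need for oxygen, and no level for patients without that need appears anywhere in the article.

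**Eligibility.** Table 2 asks for "Confirmed prior diagnosis of COPD, regardless of disease stage or ongoing therapy" and for "Admission to the ED with acute exacerbation of COPD", together with age and consent. GOLD I and ABE category A are listed as eligible. Section 2.2 adds: "Exacerbation severity will be classified at the point of care as mild, moderate, or severe". Nothing in Table 3 removes a patient because oxygen was not needed.

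**Outcome.** Section 2.3 plans a "prognostic correlation with the later need for oxygen therapy, NIV or IMV". Section 3 asks "whether higher baseline levels predict progression to supplemental oxygen, NIV, or IMV". Table 1 has a secondary objective that begins "To determine biomarker cutoff values associated with the need for escalation of respiratory support (oxygen therapy, non-invasive ventilation, or invasive mechanical ventilation", so oxygen is the first level named there.

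**Data.** Section 2.5.2 lists "oxygen therapy requirements" (mask type, flow, FiO2) among the items recorded at ED admission.

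**The concern.** A classification used for an outcome should give every enrolled patient exactly one place, and an outcome that is to be predicted needs patients who do not have it. The three-level scheme meets neither condition for oxygen. The article does not say what happens to a patient managed on room air. Such a patient could be left out of the support-level comparisons, or be placed in the oxygen group without meeting its definition. If that choice is made after the data are seen, it becomes an analyst's decision on an outcome that the article names in advance. A cut-off for need of oxygen, one reading of the Table 1 objective, could not be obtained from the three groups at all.

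**Working it through.** **Step 1. Does the scheme cover the eligible population?**

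| Source | Content | Is oxygen need required? |
|---|---|---|
| Table 2 | Age 50 or over, prior COPD of any GOLD grade or ABE category, ED admission with an exacerbation, consent | No |
| Section 2.2 | Exacerbations graded mild, moderate or severe | No |
| Table 3 | Exclusions | None refers to oxygen need |
| Section 2.5.4 | Oxygen, NIV or IMV | Yes, for every group |

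It does not. Eligible patients without oxygen need fall outside all three groups.

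**Step 2. Can need for oxygen be analysed within the three groups?** Every classified patient requires at least oxygen, so the number of non-cases is 0. Specificity is true negatives divided by non-cases, which is 0/0. The ROC curve, its AUC and any cut-off are therefore undefined for this event. This follows from the definitions alone. Contrasts between oxygen, NIV and IMV can still be estimated.

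**Step 3. The article's own power figure.** Section 2.3 gives a power of 0.91–0.92 for a two-tailed Mann–Whitney test with N = 100, d = 0.8 and alpha = 0.01. The allocation is not stated; I assume 50:50. The noncentrality is d × √(n1·n2/(n1+n2)) = 0.8 × √25 = 4.0.

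- Normal approximation: 0.923
- Noncentral t, 98 df: 0.912
- Noncentral t with sample sizes multiplied by 3/π (the efficiency of the Mann–Whitney test for normal data): 0.897

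The figure is reproduced to within 2 percentage points. It applies to an even two-group split and says nothing about an oxygen yes/no contrast.

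**Step 4. What would a fourth level offer?** Let u be the share of patients who never need oxygen. The article does not give it, so I take 5% to 40%. With N = 100 and d = 0.8, n1 = 100u and n2 = 100(1 − u), both multiplied by 3/π. For u = 20% the noncentrality is 0.8 × √((20 × 80/100) × 3/π) = 3.13. Section 2.3 uses alpha 0.01 and Section 2.5.6 uses 0.05, so both are shown.

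| u | Power, alpha 0.01 | Power, alpha 0.05 |
|---|---|---|
| 0 (as written) | not estimable | not estimable |
| 5% | 0.18 | 0.39 |
| 10% | 0.39 | 0.64 |
| 20% | 0.69 | 0.87 |
| 30% | 0.83 | 0.94 |
| 40% | 0.88 | 0.97 |

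The comparison becomes possible, but it is weak if few patients are on room air.

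**Step 5. Does leaving the level out reduce power across support levels in general?** I simulated a Spearman test of biomarker against support level with N = 100, split 20/45/25/10 over none/oxygen/NIV/IMV, at alpha 0.01. All of these are assumptions. The article assigns correlation coefficients to severity scores, not to support level.

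| Assumed biomarker pattern | Four levels | Room-air patients dropped | Merged into oxygen |
|---|---|---|---|
| Rises 0.4 SD at every step | 0.79 | 0.41 | 0.68 |
| No difference between none and oxygen, then 0.4 SD per step | 0.37 | 0.41 | 0.47 |

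The ordering reverses between the rows, so the sign of any power effect depends on a pattern that is not known.

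**The case against.** **No passage says that unclassified patients leave the study.** This stands. They remain in the primary objective (discharge status and 28-day survival), in the correlations with severity scores and in the Kaplan–Meier analysis. The gap touches only support-level analyses, which serve secondary objectives.

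**The data exist.** This stands in part. Oxygen requirements are recorded at ED admission, so a no-oxygen level can be derived for that time. The defect lies in the stated grouping, not in data capture. However, Section 2.3 speaks of later need, and an admission record alone does not settle that.

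**No stand-alone ROC analysis for oxygen yes/no is specified.** This is true of Section 2.5.6, which refers to adverse outcomes. But Table 1 names oxygen therapy within the cut-off objective, and Sections 2.3 and 3 name it as an outcome, so the reader is led to expect such an analysis.

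**Almost all patients may need oxygen.** This is possible; the article gives no share. In that case progression to oxygen could hardly be predicted and should not be listed as an outcome. The text would still need changing.

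**This belongs in the analysis plan.** I do not accept this. The article does not leave the grouping open. It fixes one that conflicts with its own eligibility criteria and its own outcome.

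**A stronger inference.** A reader might conclude that the three-group scheme costs the study power. The documents do not support that: Step 5 shows a loss under one assumed pattern and a gain under another, with a test that the article does not plan for this purpose.

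**Conclusion.** The point holds as an inconsistency between eligibility, classification and stated outcome. Two consequences follow from the text without any numerical assumption: eligible patients who never need oxygen have no group, and need for oxygen has 0 non-cases within the three groups. The scope is limited. NIV and IMV contrasts, discharge status and 28-day survival are not affected.

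The number of patients concerned is unknown. The range of 5% to 40%, and the power of 0.18 to 0.88 at alpha 0.01 that goes with it, rest on N = 100, d = 0.8 and approximately normal data. They illustrate what a fourth level could support and do not measure harm to the study. It should be corrected before analysis, but it does not undermine the primary objective.

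**What to change.** In Section 2.5.4, classify every participant into four ordered levels: no supplemental oxygen, oxygen, NIV, IMV. Keep all participants in the support-level analyses, and use the no-oxygen level as the comparator for any analysis or cut-off for need of oxygen.

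State in advance that if too few patients fall in that level, it will be reported descriptively and progression to supplemental oxygen will be dropped as a predicted outcome. Then bring Section 2.3, Section 2.5.4, Section 3 and the cut-off objective in Table 1 into line with each other.

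**Cost.** A line in Section 2.5.4, matching wording elsewhere and one extra code on the monitoring form. No additional patients or assays are needed. The level at admission can be derived from items already collected, and the code should also cover the rest of the stay, because the outcome is later need.

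**Downside.** The no-oxygen group may be small and its estimates imprecise.

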The proposed study seeks to validate the prognostic significance of resistin, CC16, IL-6, TNF-α, and S100β in a real-world emergency care population. By correlating their serum concentrations with established clinical scores, imaging parameters, and short-term outcomes, this research aims to identify biomarker thresholds predictive of mortality and ventilator support escalation. Ultimately, these findings could support the development of a biomarker-based early prognostic score, offering a precision-medicine approach to COPD management in the ED (Table 1). Specifically, we will evaluate whether baseline biomarker concentrations obtained at ED admission correlate with the subsequent level of respiratory support required during hospitalization, supplemental oxygen, non-invasive ventilation (NIV), or invasive mechanical ventilation (IMV), without influencing therapeutic decisions in real time.

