#### 2.5.3. Biomarkers Selected for Assessment in the Study

Serum concentrations of resistin, CC16, IL-6, TNF-α and S100B protein will be measured using standardized sandwich ELISA assays kits (Elabscience^®^, Biotechnology Inc., Wuhan, Hubei, China). Blood samples will be collected at ED admission into 5 mL biochemistry vacutainers with gel separator. After collection, samples will be centrifuged, at 3500 rpm and the resulting serum will be either processed fresh within a maximum of eight hours or stored at −70 °C until analysis, according to the manufacturer’s recommendations. Hemolyzed or lipemic samples will be excluded.

All assays will be performed following the manufacturer’s protocol, including reagent preparation, incubation conditions, calibration curve generation, and internal quality control verification. Optical density will be measured at 450 nm, and biomarker concentrations will be calculated using a four-parameter logistic (4-PL) curve model.

The analytical characteristics of each ELISA assay, detection range, analytical sensitivity (LOD/LOQ), intra- and inter-assay variability (CV%), assay specificity and cross-reactivity, and reference intervals for normal adult populations, are summarized in Table 4.

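### The oxygen/NIV/IMV grouping has no time point and no rule for patients already on support at the admission blood draw, yet it is read as later or escalated support

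*Protocol article*

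**What the plan says.** - **Sampling.** Section 2.5.3: "Blood samples will be collected at ED admission into 5 mL biochemistry vacutainers with gel separator". This is the only sampling time given.
- **Support at admission.** Section 2.5.2, in the list that opens "Parameters evaluated during the study at ED admission", records oxygen requirements, need for NIV with settings, and "need for IMV with ventilatory parameters, including airway resistance and lung compliance".
- **Grouping.** Section 2.5.4: "study participants will be classified into three groups: COPD patients requiring supplemental oxygen therapy, those requiring NIV, and those requiring IMV". No time point is attached, and support need not start after the draw. The next sentence nevertheless describes the result as prognostic for subsequent support.
- **Interpretation elsewhere.** The Introduction asks whether "baseline biomarker concentrations obtained at ED admission correlate with the subsequent level of respiratory support required during hospitalization". Section 2.3 speaks of later need. Table 1, first secondary objective, seeks cut-offs for escalation of support. Section 3 aims to examine "whether higher baseline levels predict progression to supplemental oxygen, NIV, or IMV".
- **A separate status.** Section 2.5.4 also classes patients as improved, stable, worsened or deceased at ED discharge or before transfer to a ward. Escalation of support is one component of worsened.

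**The concern.** A marker measured at admission can predict only what happens after admission. For a patient already on NIV or IMV at the draw, the marker describes the present state. If that patient is counted with those who step up later, the analysis answers a mixture of two questions: what the marker looks like in supported patients, and whether it foretells escalation.

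The first secondary objective is at stake, since its cut-offs are meant for escalation. Section 3 goes further and foresees thresholds that could trigger escalation of ventilation. Cut-offs derived partly from patients already ventilated would not support that use.

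The analysis section does not repair this. Its adjustment covariates do not name support level at the draw, and the ROC analysis is described for individual biomarkers, with no at-risk set.

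**Working it through.** **1. The plan's own figure.** Section 2.3 gives power of about 0.91–0.92 for a two-tailed Mann–Whitney test with 100 patients, d = 0.8 and α = 0.01. The split is not stated. With 50 against 50, the noncentrality is 0.8·√(50·50/100) = 4.0. This gives 0.9125 by the noncentral t and 0.923 by the normal approximation. With the Mann–Whitney efficiency 3/π = 0.955 it is 0.897. The figure therefore reproduces for equal groups and is not in dispute.

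**2. The order of events.**

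| Element | Time given |
|---|---|
| Blood draw (2.5.3) | ED admission |
| NIV/IMV need with settings (2.5.2) | ED admission |
| Oxygen/NIV/IMV group (2.5.4) | none |
| Interpretation (Introduction, 2.3, 2.5.4, Table 1, section 3) | after admission |

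Airway resistance and compliance under IMV are measured in a ventilated patient, so the plan expects some patients to be on IMV at or near admission. Table 3 does not exclude patients on NIV or IMV, and no other rule sets them apart. A patient ventilated at the draw can only be placed in the NIV or IMV group.

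**3. Effect on the AUC.** Compare patients ever on NIV/IMV with those never on it. Let w be the share of cases already supported at the draw. The AUC averages over case–control pairs, so

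AUC_pooled = w·AUC_prevalent + (1 − w)·AUC_incident.

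None of these inputs is in the documents. Assume AUC_prevalent = 0.75 and AUC_incident = 0.50, that is, no ability to predict later escalation:

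- w = 0.3: 0.225 + 0.350 = 0.575
- w = 0.5: 0.375 + 0.250 = 0.625
- w = 0.7: 0.525 + 0.150 = 0.675

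In simulation with 30 or 40 cases among 100, the chance of p < 0.05 in these settings ran from 0.20 to 0.86.

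Using the plan's d = 0.8 for the prevalent cases instead, AUC_prevalent = Φ(0.8/√2) = 0.714. The pooled AUC is then 0.554, 0.607 and 0.661 for w = 0.25, 0.50 and 0.75.

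**4. Sensitivity.**

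- With w = 0.1 and AUC_prevalent 0.75, the pooled AUC is 0.075 + 0.450 = 0.525 and rejection is 0.06–0.07, close to the nominal 0.05.
- With AUC_prevalent 0.60 and w = 0.3–0.7, the pooled AUC is 0.53–0.57 and rejection is 0.07–0.22.
- If AUC_prevalent were below AUC_incident, the formula would pull the pooled value down, not up.

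**5. Power once only later cases count.** The comparison is n₁ later-onset cases against n₂ patients never on NIV/IMV, with noncentrality 0.8·√(0.955·n₁n₂/(n₁+n₂)), d = 0.8 and α = 0.01. The numbers ever supported are assumed.

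| Ever on NIV/IMV | All counted | 25% already supported | 50% | 75% |
|---|---|---|---|---|
| 30 of 100 | 0.827 | 0.722 | 0.545 | 0.278 |
| 40 of 100 | 0.882 | 0.803 | 0.650 | 0.365 |

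For example, with 30 ever supported and half already supported, n₁ = 15 and n₂ = 70. The noncentrality is 2.75 and power is 0.545.

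**The case against.** The strongest reply is that the plan says repeatedly that it means subsequent support, including in the sentence right after the grouping. A reader might infer that existing support is deliberately counted as outcome, or that anyone supported at any time enters the group. No sentence states either rule. What stands is narrower: the intent is clear, but the grouping as written does not deliver it.

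A reader might also infer from section 2.5.2 that NIV and IMV are shown to precede the sample. That list also holds urine output, the end-tidal CO₂ trend and medication given in the ED, which extend over the ED stay. The order of draw and support is therefore unclear, not shown to be reversed. Home oxygen as baseline support is not mentioned at all.

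A third inference is that secondary objective 1 goes wholly unanswered. The worsened status is change-based and could serve during the ED stay. It covers the objective only in part, because it is a composite and stops at ED discharge or transfer, while the Introduction refers to support during hospitalization.

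Table 3 excludes patients unable to consent, which might remove some who arrive intubated. Table 2 and section 2.4 allow consent by a legal representative, so this is no dependable filter.

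Finally, a condensed article may leave at-risk sets to a fuller document. That would answer an omission. Here the article states both the grouping and its interpretation, and the two do not match.

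**Conclusion.** The point holds as a mismatch between an undated grouping and a prospective interpretation. It is confined to the respiratory-support analyses and their cut-offs. Patients whose support starts after the draw still give a true prospective comparison, and 28-day survival is not affected.

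That part of the association would be cross-sectional follows from the text, provided some patients are on NIV or IMV at the draw. That the AUC would be inflated does not follow from the text alone: it requires the marker to track current support more strongly than later escalation. That is plausible for inflammation and injury markers, but it is assumed. The size cannot be fixed from the documents. It runs from almost nothing at 10% already supported to a pooled AUC of 0.675 from a marker with no predictive value at 70%.

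**What to change.** - Record the support level at the blood draw and whether each form of support began before or after it. Most of this is already collected under section 2.5.2; the added item is timing relative to the draw.
- Define escalation as a step above that level, after the draw, within a stated window.
- Restrict each escalation analysis and its ROC cut-off to patients still at risk of that step. A patient on IMV at the draw leaves the at-risk set; one on NIV is at risk of IMV only.
- Report the association with support at the draw separately and label it cross-sectional.
- Reconcile sections 2.5.2 and 2.5.4 with the Introduction, section 2.3, section 3 and Table 1, and say how the worsened status relates to the escalation outcome.

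The cost is wording, one timing field, fewer events and wider intervals. The stated power of 0.91–0.92 does not carry over to the smaller set and should not be cited for it. The timing has to be captured during enrolment, since the order of draw and support may not be recoverable afterwards.
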